#### Interventions: adherence to intervention protocol

Inclusion and exclusion criteria will be strictly adhered to. The questionnaires shall be checked for completeness and accuracy of the data. The research assistants (doctors on duty) will be adequately trained and routinely supervised by the principal investigator and study supervisors to ensure correct use of data collection tools and adherence to ethical principles.

#### Interventions: concomitant care

No relevant concomitant care or interventions will be prohibited during the study.

#### Outcomes measures

The following outcome measures were selected based on existing literature and will be reported in conformity with Zarin et al. [26].

### Primary outcome measures

The primary outcome measures will be early 30-day post-operative complications (harms), including: pain, nausea, vomiting, hematoma, transient voice changes, and surgical site infection rates.

The complications will be reported verbally to nursing or to attending physicians for evaluation and recorded on a questionnaire in accordance with MedDRA® version 4.21 standardized reporting on medical and surgical procedures. The post-operative pain will be measured based on visual analogue scale of 0–10 where 0 means no pain and 10 means the worst possible pain. The pain will be assessed at an interval of 6, 12, and 24 h and at 30 days. The mean pain scores will be compared at using Student’s *t*-test, assuming normal distribution; otherwise, medians will be compared using non-parametric Kruskal–Wallis rank sum test.

The nausea and vomiting will be reported to nursing or attending physicians and recorded to the questionnaire using a nausea score on a scale of 0–9 where 0 means no symptom and 9 means very severe. The symptoms will be assessed at an interval of 6, 12, and 24 h and at 30 days. The mean nausea scores will be compared using a paired Student’s *t*-test, assuming normal distribution; otherwise, medians will be compared using non-parametric Kruskal–Wallis rank sum test.

Complications: hematoma, transient voice changes, and surgical site infection rates will be assessed at 6, 12, and 24 h and at 30 days will be reported in accordance with the Clavien Dindo classification of surgical complications [27], where grade I represents complications that do not require any additional intervention, grade II requires pharmacological treatment but not radiological or surgical intervention for instance blood transfusion, grade III requires radiological or surgical re-intervention, e.g., neck exploration and hematoma evacuation, grade IV representing life-threatening complications with at least one organ dysfunction such as respiratory failure that requires intensive care admission. The difference in proportions will be compared using Wilcoxon sum rank test.

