**Discussion:**

The primary outcome of this trial protocol is to compare the early post-operative complications of euthyroidectomy done under LA versus GA. The outcome variables include post-operative pain based on visual analogue scale, nausea, vomiting, hematoma formation, and transient voice changes determined at an interval of 6, 12, and 24 h and at 30 days.

In addition, we shall compare the surgical site infection rates, procedure costs, hospital stay, and patients’ level of satisfaction based on a 5-point Likert scale and their willingness to undergo a similar surgery using the same anesthetic technique between the two groups. We hypothesize that euthyroidectomy under LA could potentially offer similar benefits as GA, reduce costs related to procedure, complications, and hospital stay while at the same time mitigating the unmet need for surgery attributable to shortage of general anesthesia providers and critical care facilities in low-income settings.

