### Specific objectives

The specific objectives of this study are as follows:To compare the occurrence rates of early 30-day post-operative complications (pain, hematoma, surgical site infection) following euthyroidectomy under LA versus GATo compare the cost implications of euthyroidectomy under LA versus GATo compare the patients’ level of satisfaction for euthyroidectomy under LA versus GA

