### Sample size estimation

Sample size estimation in this study assumes a null hypothesis that there is no difference in early post-operative outcomes for euthyroidectomy under LA versus GA (equivalence study). In a study that evaluated the measurement of acute post-operative outcomes amongst patients who undergo surgery, a patient acceptable symptom state, i.e., the value beyond which patients considered themselves well, was documented at 33% [28]. Based on a study at the Scott and White Memorial Hospital, in Texas, the proportion of patients who underwent euthyroidectomy under LA with no identifiable complication were 83% as opposed to 79% who underwent GA [16]. Therefore, assuming a statistical power of 80%, type 1 error of 0.05, and a threshold for equivalence in effect with a dichotomous outcome that LA is no better or worse than GA by a minimal clinically important difference of 33% in the primary outcome measures; the sample size estimation based on Cleveland Clinic sample size estimation in clinical research (https://riskcalc.org/samplesize/) [29] will be 26 for each arm (1:1 allocation), including additional 10% to cater for loss to follow-up.

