## Objective one

The occurrence of early post-operative complications of euthyroidectomy under the two arms (LA and GA) of the study will be measured by total occurrence of a particular complication divided by the total number of euthyroidectomy done under LA and GA, respectively. These will be expressed as percentages with 95% confidence interval and the difference in proportions will be compared using a two-sample Student’s *t*-test, assuming normal distribution and equal variance. The Shapiro–Wilk test will be used to assess for normalcy of distribution whereas Levene’s test will be used to assess for equality of variance.

For the pain scores, visual analogue scale will be stratified as no pain (0), mild (1–3) or moderate (4–6), and severe (7–10) and the difference in proportions will be compared using non-parametric Kruskal–Wallis rank sum test (H). The overall occurrence of adverse events in both groups will be summarized as proportions in accordance with Clavien Dindo classification [27].

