### Data monitoring committee and auditing for harms

#### Interim analysis

The Kampala International University Western Campus Research and Ethics Committee will form an interim committee that will audit this study and have access to results of interim analysis which will be performed when the 30th patient is recruited (58% of total sample size). The committee will independently recommend continuation, modification, or termination of the study in accordance with its ethical guidelines in relation to safety of human research participants.

Such circumstances warranting termination include unbearable adverse effects or in the unlikely event of achieving differences between study groups. Otherwise, comprehensive results would be published in the final stages of dissemination.

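### No single contrast decides the trial: six complications are primary and tested separately for difference, while the proportion sized for equivalence is given no test

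*Protocol article*

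**What the plan says.** - **Primary outcome measures.** The article states: "The primary outcome measures will be early 30-day post-operative complications (harms), including: pain, nausea, vomiting, hematoma, transient voice changes, and surgical site infection rates". For pain it adds: "The pain will be assessed at an interval of 6, 12, and 24 h and at 30 days". The same four times are given for nausea and vomiting, which are recorded on one nausea score, and for the other complications. Mean scores are compared by a t-test or Kruskal–Wallis, the remaining complications by a Wilcoxon test.
- **Objective one.** Occurrence is "measured by total occurrence of a particular complication divided by the total number of euthyroidectomy done under LA and GA, respectively", and these proportions are compared by a two-sample t-test. Pain appears again, now in severity strata compared by Kruskal–Wallis. Overall occurrence of adverse events is summarised by Clavien–Dindo grade, with no test and no margin.
- **Other versions of the list.** Specific objectives has three items: "early 30-day post-operative complications (pain, hematoma, surgical site infection". The Discussion paragraph of the Abstract has five: "post-operative pain based on visual analogue scale, nausea, vomiting, hematoma formation, and transient voice changes". There, surgical site infection is set apart, next to cost, stay and satisfaction.
- **Sample size estimation.** One dichotomous outcome is used, freedom from complications (83% LA, 79% GA), with 80% power and type 1 error 0.05. The equivalence threshold is then expressed "by a minimal clinically important difference of 33% in the primary outcome measures", in the plural.
- **Data management and analysis.** One confidence level (95%) and one significance threshold serve every analysis.
- **Interim analysis.** At the 30th patient, one ground for termination is "in the unlikely event of achieving differences between study groups", with no outcome named.

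**The concern.** The sized contrast is given no test, and the tested contrasts were never sized. The trial is labelled an equivalence trial, but the comparisons assigned to the primary outcomes are all tests of difference.

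The outcomes may also diverge. The Introduction cites studies with less pain under LA and one with higher pain scores under LA. If one pain comparison is significant while overall complication rates are close, the plan does not say whether the trial found equivalence or a difference. Either report could be defended from the same data.

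The margin cannot be carried across the list either. Thirty-three percentage points is a difference between proportions. It has no meaning for a mean on a 0–10 pain scale or a 0–9 nausea scale.

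**Working it through.** **1. What the sample size supports.** Inputs from Sample size estimation: 0.83, 0.79, margin 0.33, alpha 0.05, power 80%, 10% loss.

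- Variance term: 0.83×0.17 + 0.79×0.21 = 0.1411 + 0.1659 = 0.3070.
- With one-sided 0.05 and true difference 0.04: n = 0.3070 × (1.645 + 0.842)² / (0.33 − 0.04)² = 0.3070 × 6.18 / 0.0841 ≈ 22.6, so 23 per arm.
- Allowing for loss: 23 / 0.90 = 25.6, so 26 per arm, as stated.

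The stated 26 therefore follows from one proportion judged once against the margin. (This form powers one side of the margin only, which is a separate matter.) It says nothing about six outcomes or about mean scores.

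**2. Number of tests.** The article does not fix it.

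- Six complications with one test each give 6. If nausea and vomiting share one test, the count is 5.
- Six complications at four times would give 6 × 4 = 24. The article says the outcomes are assessed at those times, not that each time is tested, and Objective one uses total occurrence. So 24 is an upper bound.

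**3. Chance of at least one false difference.** Each test is two-sided at 0.05, the type 1 error in Sample size estimation. The threshold printed in Data management and analysis is 0.5, a separate error that is not used here.

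- Independent tests: 1 − 0.95^k. For k = 5, 22.6%; for k = 6, 26.5%; for k = 24, 70.8%.
- Correlated tests: simulation of k normal test statistics with a common correlation, counting runs with any |z| > 1.96. The correlation is an assumption.

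| Assumed correlation | 6 tests | 24 tests |
|---|---|---|
| 0 | 26.5% | 70.8% |
| 0.3 | 24.1% | 59.4% |
| 0.5 | 20.8% | 45.8% |
| 0.7 | 16.4% | 30.9% |
| 0.8 | 13.7% | 23.9% |

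**4. Effect of rare events.** The Introduction puts complications such as hematoma and surgical site infection below 4% under LA. At 26 per arm and an assumed 4% in both arms, a t-test on a proportion rejects only about 1.3% of the time. Patients were then simulated with three continuous scores and three binary complications over a range of correlations:

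- all three binary complications at 4%: 16% to 18% for six tests, 30% to 54% for 24;
- voice change at an assumed 15%, the other two at 4%: 19% to 21%, and 37% to 61%.

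Even 16% is about three times 5%.

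**The case against.** The strongest defence is that the primary outcome is a single composite of early complications, that its listed items are components, and that multiplicity rules belong in an analysis plan that is not shown. The second half has force: the absence of a detailed multiplicity procedure would not by itself be a finding. The composite reading does not survive the text. The heading and its sentence are plural, each item has its own test, Objective one works complication by complication, and overall occurrence is only summarised. A composite could not be computed as things stand, because no cut-off says when a pain or nausea score counts as a complication. What is wrong here is how the stated primary outcomes, tests and sample size fit together, and the protocol itself fixes all three.

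A second objection is that in an equivalence trial the type 1 error is a false claim of equivalence, so a false-difference rate is not the alpha used for sizing. That is correct, and the percentages above should not be read as inflation of that alpha. They matter because the planned tests are tests of difference and the interim wording refers to differences.

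Three stronger readings are tempting and are not supported:

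- **A single inflation figure, such as 21% or 46%.** Each needs an assumed correlation of 0.5, and the second also needs 24 tests.
- **Low joint power if equivalence had to be shown on all six.** No such rule is stated, and 80% power cannot be assumed for each outcome. At an assumed 4% in both arms and 23 evaluable per arm, the standard error is √(2×0.04×0.96/23) = 0.058. A 0.33 margin is then about 5.7 standard errors, so power is above 99%. For mean scores the margin, and hence the power, is undefined.
- **That a difference on any contrast can stop the trial.** The Interim analysis section names no contrast and describes a committee recommendation made under ethical guidelines on participant safety.

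**Conclusion.** The point holds as a mismatch between stated rules. Six complications are primary in the outcome section, five in the Abstract and three in the Specific objectives. They receive separate unadjusted difference tests, and nothing says which result decides. The outcome that determined the sample size is outside the primary list and has no test against its margin, so the equivalence question is not answered by the analysis as written.

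The chance of at least one false difference is about 14% to 27% for six tests. It is about 24% to 71% for 24, if every outcome-by-time contrast were tested. Both ranges assume two-sided 0.05 and a common correlation between 0 and 0.8. Sparse events reduce them, and a correlation above 0.8 would reduce them further. The mismatch is certain from the text; the percentages are only as firm as these assumptions. It should be settled before results are compared by arm.

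**What to change.** - **One primary contrast.** In Primary outcome measures, Sample size estimation and Objective one, name the LA-GA difference in the proportion with no complication by day 30, judged by a confidence interval against the stated equivalence margin. Replace the plural attached to the margin with this outcome.
- **Definition.** State what counts as a complication, including a cut-off for the pain and nausea scores. Do so before unblinding; the Blinding section keeps the statisticians blinded only until the interim analysis. Confirm that the 83% and 79% planning rates apply to that definition.
- **Lists.** Make the Abstract, the Specific objectives and Primary outcome measures agree. Make individual complications and scores at each time secondary, reported as estimates with confidence intervals.
- **Interim.** State which contrast the difference-based ground for termination refers to, and that any such stop accounts for the interim look. Leave the safety review unchanged.

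**Cost.** No new data are needed, but more than one sentence must change: a composite definition has to be written. If the planning rates do not fit it, the sample size must be recalculated. Results on a single complication or time point can no longer be claimed as confirmatory.

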### Data management and analysis

Data will be coded, entered in Excel version 2016, and later exported to STATA 14.2. for analysis. The intention-to-treat model will be used to minimize bias as way of reflecting what happens in real clinical practice. The intention-to-treat population will be used for inference and will be defined as all eligible randomized patients recruited in this study. Analysis will be done per study objective. Socio-demographic and surgical factors will be summarized descriptively using summary measures as proportions, means, medians, and measures of variation such as standard deviations for means, interquartile range for medians. All analyses will be computed at 95% confidence intervals and regarding *p* < 0.5 as statistically significant.

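### Pain and nausea are primary scores taken at four times, but the plan fixes only one-off tests and does not say which comparison decides

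*Protocol article*

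**What the plan says.** Under Primary outcome measures, pain on a 0–10 visual analogue scale is a primary outcome: "The pain will be assessed at an interval of 6, 12, and 24 h and at 30 days. The mean pain scores will be compared". The sentence then names Student's t-test if the scores are normal and Kruskal–Wallis otherwise. It is broken just before the test is named: a preposition is left without an object, so a time point or other words may have dropped out.

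Nausea, on a 0–9 scale, follows the same schedule: "The symptoms will be assessed at an interval of 6, 12, and 24 h and at 30 days". Its first-line test is a paired t-test, with Kruskal–Wallis as the fallback.

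Objective one adds a second pain analysis. The scale is cut into none, mild, moderate and severe, and "the difference in proportions will be compared using non-parametric Kruskal"–Wallis. No time is named there either.

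The SPIRIT timeline (Table 1) confirms four post-operative assessments. The article gives no primary time, no single value per patient, no model term for patient or time, and no rule for combining the four results.

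The sample size section works from "assuming a statistical power of 80%, type 1 error of 0.05".

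**The concern.** The patient is randomised once and measured four times. A t-test or a Kruskal–Wallis test compares one value per patient between arms, and the plan does not say what that value is. Followed as written, the analyst must choose between testing each time separately, entering all scores together, or picking a time or summary that the protocol does not name.

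Separate testing gives four chances per score to report a difference, with no rule for what happens if 6 h and 24 h disagree. Entering all scores together treats one patient's correlated values as if they came from different patients. In both cases, the precision available from averaging several early scores in the same patient is lost.

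This matters because these are primary outcomes and the tests named for them are difference tests. The Interim analysis section also lists a difference between the groups among the circumstances that could end the trial.

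**Working it through.** **Inputs from the Protocol article.** Four scores per patient; 26 per arm (Sample size estimation; the abstract gives 29); two-sided 5% level, from the type 1 error in the same section. **Assumptions.** The article gives no within-patient correlation ρ, so 0.3, 0.5 and 0.7 are used, equal for all pairs of times. Scores are normal and there is no true difference.

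**Step 1. The plan's own figure.** The inputs are the proportions "with no identifiable complication were 83% as opposed to 79% who underwent GA", a margin of 33 percentage points, and 80% power. For equivalence with one-sided 5% tests:

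n = [0.83×0.17 + 0.79×0.21] × (1.645 + 0.842)² / (0.33 − 0.04)² = 0.307 × 6.18 / 0.0841 = 22.6, so 23. Adding 10% for loss: 23/0.9 = 25.6, so 26. The stated 26 per arm is reproduced. It is built on a yes/no outcome and says nothing about repeated scores.

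**Step 2. A separate test at each of four times.** If the tests were independent, the chance of at least one p < 0.05 would be 1 − 0.95⁴ = 18.5%. Correlation lowers this. Simulation with 26 per arm (20,000 runs per setting):

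| ρ | each single test | at least one of four |
|---|---|---|
| 0.3 | 5.0% | 17.6% |
| 0.5 | 5.0% | 15.8% |
| 0.7 | 5.0% | 13.1% |

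Each test is valid alone. The excess comes from having four of them.

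**Step 3. All scores pooled as independent (4 × 26 = 104 per arm).** With the same mean and variance at each time, the variance of an arm mean is understated by the factor 1 + 3ρ, so the error is 2[1 − Φ(1.96/√(1+3ρ))]:

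- ρ = 0.3: 1.96/1.378 = 1.422, giving 15.5% (simulated 15.7%)
- ρ = 0.5: 1.96/1.581 = 1.240, giving 21.5% (simulated 21.9%)
- ρ = 0.7: 1.96/1.761 = 1.113, giving 26.6% (simulated 27.0%)

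The formula does not depend on the number per arm, so 26 versus 29 makes no difference to it.

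If scores fall over time, the trend enlarges the pooled standard deviation and offsets the inflation. With illustrative means of 5, 4, 3 and 0.5 and SDs of 2, 2, 1.7 and 0.7, the simulated error is 2.6% (ρ = 0.2), 3.8% (0.3), 6.7% (0.5) and 10.2% (0.7). Pooling therefore leaves the error uncontrolled in either direction.

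**Step 4. One value per patient.** A t-test on a per-patient mean has simulated error of about 5% at each correlation: 4.8–5.1% for the mean of all four scores and 4.9–5.1% for the mean of the three early ones.

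**Step 5. Power for an assumed 0.6 SD difference at every early time.** One time alone gives about 56–57%. The mean of three scores has variance (1 + 2ρ)/3, so the standardised difference becomes 0.6/√[(1 + 2ρ)/3]:

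- ρ = 0.3: 0.6/0.730 = 0.82, power 83%
- ρ = 0.5: 0.6/0.816 = 0.73, power 74%
- ρ = 0.7: 0.6/0.894 = 0.67, power 66%

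**The case against.** The strongest reply is that the pain sentence is damaged. A time point may be missing from it, and a comparison of mean scores could mean one mean per patient. On either of those readings the error is about 5%. That stands, so it cannot be said that the text forces an inflated error. What remains is that no time or summary is actually named, there or under Objective one.

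A reader might infer that 104 scores per arm will be pooled, or that the nominal 5% simply becomes 13–27%. The document supports neither. Pooling is never stated. The correlation is assumed. The two ends of that range are different quantities: 13% is the chance of any positive among four valid tests, and 27% is the error of one invalid test under stable means. With falling scores the pooled error may be below 5%.

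A reader might also group nausea with pain as analysed by tests for independent observations. Only nausea's Kruskal–Wallis fallback fits that. Its first-line test is paired, a separate problem because parallel arms supply no pairs. The missing time or summary applies to nausea all the same.

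It is also fair to say that the trial is designed for equivalence, "LA is no better or worse than GA by a minimal clinically important difference of 33% in the primary outcome measures", so these rates are not the type I error of an equivalence conclusion. They are still the error rates of the tests the protocol names for these scores.

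Finally, time points and repeated-measures models are often left to an analysis plan. Here, however, the protocol does fix tests, two different ones for pain, and they do not fit four-times-measured scores unless a single value is defined.

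**Conclusion.** The point holds as a gap in what the protocol fixes for two primary scores. One-off tests are specified for outcomes measured four times, with nothing to say which comparison decides.

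On the most natural reading, a test at each time, the chance of at least one false difference is about 13–18% per score, while each test keeps 5%. This assumes normal scores, 26 per arm and ρ from 0.7 to 0.3. Pooling, if it were done, would give about 16–27% with stable means and variances, or about 3–10% under the illustrative falling profile.

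All figures use a 5% threshold, as in the sample size section. Data management and analysis states a different one ("All analyses will be computed at 95% confidence intervals and regarding *p* < 0.5 as statistically significant"), a conflict that needs its own correction. The change should be made because it concerns primary outcomes and costs little, but the document does not show that the error rate is necessarily inflated.

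**What to change.** In Primary outcome measures and Objective one, define one pre-named between-arm contrast for pain and one for nausea, each reported as a mean difference with its confidence interval. Two forms serve:

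- the per-patient mean of the 6, 12 and 24 h scores, compared once between the randomised arms; or
- a linear mixed model with arm, time, arm-by-time and a patient random effect, taking the arm contrast averaged over 6–24 h as the single primary estimate.

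Report the individual times, day 30 and the pain strata as supportive. Repair the broken pain sentence at the same time.

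The scores are already being collected, so only wording changes, though it does settle what the primary quantity for each score is and moves day 30 to a supportive role. The downside is small: a difference confined to one time is diluted in the average, but it stays visible in the per-time results. The choice should be made before anyone sees results by arm.

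### Vomiting is a primary outcome separate from nausea, but its stated record is a shared 0–9 nausea score that cannot give the proportion of patients who vomited

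*Protocol article*

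**What the plan says.** The Primary outcome measures section defines the primary outcome as "early 30-day post-operative complications (harms), including: pain, nausea, vomiting, hematoma, transient voice changes, and surgical site infection rates". Nausea and vomiting are two entries in that list of six. The Discussion part of the Abstract also lists them separately: "nausea, vomiting, hematoma formation, and transient voice changes determined at an interval of 6, 12, and 24 h and at 30 days".

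How the two symptoms are recorded is stated once, for both together: "The nausea and vomiting will be reported to nursing or attending physicians and recorded to the questionnaire using a nausea score". The same sentence gives the scale: "recorded to the questionnaire using a nausea score on a scale of 0–9 where 0 means no symptom and 9 means very severe". On timing, "The symptoms will be assessed at an interval of 6, 12, and 24 h and at 30 days". The analysis attached to this record is "The mean nausea scores will be compared using a paired Student’s *t*-test, assuming normal distribution", with a rank test on medians as the fallback. (A paired test for two independent arms is a separate matter and is not pursued here.)

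The same section also has a general reporting sentence for all the listed outcomes: "The complications will be reported verbally to nursing or to attending physicians for evaluation and recorded on a questionnaire", using MedDRA.

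The section headed Objective one says that the occurrence of complications in each arm will be "measured by total occurrence of a particular complication divided by the total number of euthyroidectomy", given as a percentage with a 95% confidence interval.

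**The concern.** The outcome list and Objective one treat vomiting as an event: a patient either had it or did not. The sentence that says how vomiting is recorded gives a severity grade labelled as a nausea score. These are different quantities, and the second does not determine the first.

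The Introduction names post-operative nausea and vomiting among the outcomes reported as less frequent under local anesthesia, so vomiting is a component on which a real difference between arms is plausible. The design is an equivalence trial. If vomiting events are merged with nausea, or go unrecorded, a true difference can shrink and the result can drift towards equivalence.

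A later analysis plan cannot repair this. If the form holds only a shared score, the event cannot be recovered after data collection.

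**Working it through.** The point concerns definitions, so the main check sets the sections side by side.

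**1. Does the plan need a yes/no vomiting event?** Yes, on two counts.
- Objective one divides the number with a particular complication by the number operated in that arm.
- Sample size estimation works with a dichotomous outcome: 83% (LA) and 79% (GA) with no identifiable complication, a margin of 33 percentage points, 80% power and alpha 0.05. The stated 26 per arm reproduces from these inputs with a one-sided 0.05:
  - variance term: 0.83 × 0.17 + 0.79 × 0.21 = 0.1411 + 0.1659 = 0.3070
  - n = 0.3070 × (1.645 + 0.842)² / (0.33 − 0.04)² = 22.57, rounded up to 23
  - with 10% loss: 23 / 0.9 = 25.6, rounded up to 26

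This confirms that the trial is sized on complication present or absent. It has no other bearing on the point.

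**2. What does the stated record supply?**

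| Outcome | Stated record | Stated comparison |
|---|---|---|
| Pain | 0–10 scale | mean or median; also four severity bands in Objective one |
| Nausea | 0–9 nausea score | mean or median |
| Vomiting | the same 0–9 nausea score | none of its own |
| Hematoma, voice change, surgical site infection | Clavien-Dindo grade | proportions |

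The comparison of proportions that closes Primary outcome measures belongs to the last row and does not include vomiting. Objective one gives bands for pain but no threshold for the nausea score.

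**3. Could a threshold on the score recover vomiting?** Take two patients at one assessment who rate their nausea the same, say 5. One has vomited and the other has not. Any rule of the form *score at or above c* puts both in the same class, so it either counts a non-vomiter or misses a vomiter. This holds for every c. On the most generous reading, where 0 means neither symptom at any time since the last contact, the score gives only an upper bound: the proportion who vomited cannot exceed the proportion scoring above 0.

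**4. What period does each assessment cover?** Primary outcome measures and the SPIRIT timeline table (Table 1) both put the first complication assessment at 6 h. Neither gives a look-back period.
- Point-in-time reading: a patient who vomited at 2 h and is well at 6 h can score 0.
- Look-back reading: the 6 h score covers 0–6 h and the episode counts towards it, though still merged with nausea.

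The text does not choose between these.

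**5. Illustration only.** Let v be the proportion of GA patients who vomit and r the share of those whose vomiting is over by 6 h and is recorded by no other route. The number missed in an arm of 26 is 26 × v × r. The document gives neither v nor r.
- r = 0 (the score looks back, or verbal reporting works): 0 patients.
- v = 0.20, r = 0.5 (assumed): 26 × 0.10 = 2.6.
- v = 0.40, r = 0.5 (assumed): 26 × 0.20 = 5.2.

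The range is therefore 0 to about 5. The document does not support the top of it: its only GA complication figure is 100% − 79% = 21% with any complication, in a source whose definition is not given.

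**The case against.** The strongest reply is that the nausea score is not the only route. The general sentence in Primary outcome measures has listed complications reported verbally and entered on the questionnaire, and it is not limited to 6 h or later. A vomiting episode in recovery could be entered that way. The Data collection section says that Part D of the questionnaire is completed post-operatively and during follow-up, but its items are not shown and it may already hold a vomiting line. The 6 h assessment may also look back to the end of surgery. Finally, the parenthesis in Specific objectives names pain, hematoma and surgical site infection, not vomiting.

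Much of this stands. A reader might infer that vomiting has no usable measurement, that its occurrence cannot be derived at all, or that early episodes are lost. The document supports none of these: a second recording route exists, the form is unseen, and the look-back period is open.

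It does not dispose of the point. The general sentence covers all six outcomes and sets no vomiting item, time or definition. The sentence specific to vomiting does say how it is recorded, and it names the nausea score. This is a stated rule that does not fit its purpose, rather than form detail that a condensed article leaves out. The shorter list in Specific objectives does not remove vomiting from the primary outcome, where both the Abstract and Primary outcome measures put it.

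**Conclusion.** The point holds in limited form. For one of the six named primary outcomes, in both arms and at all four assessments, the stated record does not by itself yield the per-complication proportion that Objective one requires, and no comparison specific to vomiting is stated. This follows from the text and needs no assumption about event rates.

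That the period covered by each assessment is unstated is also plain from the text. That episodes before 6 h are missed is conditional: it needs the point-in-time reading and no capture by verbal report.

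A reader might go further and infer a bias towards equivalence of a particular size. The document does not support a size. The figure of 0 to about 5 of 26 GA patients rests on assumed rates, has zero as its lower end, and should not be quoted as an estimate. The matter is worth correcting because the remedy is nearly free and must be in place when data are collected.

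**What to change.** Keep the 0–9 score and use it for nausea alone. At each scheduled assessment add one separate item: *vomited since the end of surgery* (6 h form) or *since the last assessment* (12 h, 24 h and 30-day forms), *yes/no*. The 6 h form then covers 0–6 h and the later forms follow on without gaps. State in Primary outcome measures the period to which the nausea score refers.

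Define the vomiting outcome as any episode recorded on these items, and compare it between arms as a proportion with its confidence interval, in line with Objective one. If Part D already has such an item, the change is only to say so in the text and to name the comparison.

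The cost is one extra line on the existing questionnaire, at contacts already planned. No visit is added and patient care is unchanged. Forms already completed without the item cannot be reliably filled in afterwards, so any patients assessed before the change should be reported as such.
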